### Ethics Approval

The Informed Consent process and all other study procedures were reviewed and approved by the University of Notre Dame institutional review board (protocol 21-06-6662). Additionally, in-country ethical approval was obtained from the Navrongo Health Research Center institutional review board (App/Focused-PPC/7/2021). Approval to conduct the study has also been obtained from both the regional and district levels of the GHS. All project team members have current human subject training. Informed consent will be obtained from all participants.

## Results

In the first 6 months of the project, we will complete start-up activities inclusive of inception meetings with GHS representatives at the district and regional levels, developing training guides and Focused-PPC education content, training project staff, and developing data collection tools. In the next 6 months of the project, we will recruit and enroll participants, begin Focused-PPC intervention sessions, and complete data collection. Focused-PPC intervention sessions and data collection will continue in year 2 of the project. End-line focus group discussions will be conducted with project participants and midwives when groups have completed their final intervention sessions at 12 weeks.

Ethical approval was successfully obtained from the Navrongo Health Research Center, and the appropriate approvals were obtained from the GHS. The Focused-PPC Guide (education and session guide) was successfully developed with input from GHS and evidence-based resources and underwent multiple levels of expert review to produce the final guide. All team members, midwives, and project assistants have been trained in the study protocol. Measures for data collection were successfully translated into Dagbani (the local language), and audiovisual resources for the sessions were developed and translated into Dagbani. Clinical trial registration is completed at ClinicalTrials.gov (NCT05280951).

We have enrolled and conducted baseline surveys for 192 women (sample size met) in the Focused-PPC trial who have been randomized into intervention and control arms. We have established a total of 12 Focused-PPC groups in the intervention arm, 3 groups from each site, all of which have sessions underway. Midwives are successfully conducting Focused-PPC sessions using the study’s established guide and protocol. The Focused-PPC intervention is maintained and monitored through fidelity checklists, which are specific to each time point and completed by project assistants and midwives at every session. Project assistants are also documenting sessions through photos, videos, and session reports, addressing participant actions, discussions, and collaboration.

## Discussion

### Principal Findings

The purpose of this study is to implement and evaluate a postpartum care model entitled Focused-PPC in a parallel randomized controlled trial with 192 postpartum women at 4 health centers in Tamale, Ghana. Focused-PPC sessions are underway in all participating health facilities. The primary outcome is knowledge of post-birth warning signs. We expect that the Focused-PPC group will have higher knowledge of post-birth warning signs than the control group at every time point measured and that the Focused-PPC group will have a larger increase in knowledge of postbirth warning signs between time points. We are also measuring postpartum health behaviors such as eating a healthy diet, uptake of family planning, breastfeeding, and so on. We expect that more participants in the Focused-PPC groups will eat a balanced diet most days of the week and uptake family planning compared to participants in the control groups. Additionally, we also expect mental health outcomes such as positive depression screens to be significantly lower over time in the Focused-PPC group compared to the control group. Other descriptive outcomes include postpartum health status, and we expect to capture and treat blood pressure cases during the course of the study.

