The primary outcome is knowledge of postbirth warning signs, measured through questions developed based on an evidence-based assessment of the most common postbirth complications. The secondary outcome is postpartum health behaviors, including specific questions assessing health behaviors tailored to the specific time frame postpartum. Other descriptive outcomes include postpartum health status, which will include measures of postpartum depression, stress, complications experienced, vital signs, and other questions on health status as appropriate to the time frame after delivery. Postpartum depression is measured through the Edinburgh Postnatal Depression Scale (EPDS), a self-report screening tool commonly used in perinatal settings [34,35]. The EPDS consists of 10 items assessing women’s depressive symptoms over the past week. The EPDS has a maximum score of 30, with higher scores indicating higher frequency and increased severity of depressive symptoms. Stress is measured through the Perceived Stress Scale (PSS), a 10-item scale assessing women’s stress levels over the last month [36]. The PSS evaluates a woman’s perceptions of unpredictability, lack of control, and overloading in her life, with a higher score indicating higher levels of perceived stress. The feasibility and acceptability of the intervention will be measured using end-project focus group discussion data obtained from midwives and participants in the intervention arm. Outcomes and time points of data collection can be found in Table 1.

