### Analysis Plan

Differences in outcomes between the intervention and control arms will be assessed. We expect that the intervention arm will have higher knowledge of postbirth warning signs than the control arm at every time point measured and that the intervention arm will have a larger increase in knowledge of postbirth warning signs between time points. We expect postpartum health behaviors to be different between the intervention and control arms.

All data will be reviewed for completeness and transferred to STATA (StataCorp) statistical software for analyses [37]. The primary variable of interest is knowledge of postbirth warning signs, measured on 4 occasions. The baseline measurement of knowledge of postbirth warning signs will be used in an initial *t* test to confirm that there is no difference in knowledge between the intervention and control arms before the study to validate the randomization procedure. We will model and test the difference between intervention and control arm knowledge of postbirth warning signs at each time point, and knowledge between time points will be assessed using a repeated measures multivariate ANOVA (MANOVA) with a time and treatment interaction as the primary analysis controlling for baseline demographic variables. For the intervention arm, follow-up secondary analyses will measure the change in postpartum health status, postpartum health behaviors, and clinical assessment data over time using repeated measures MANOVA. Ancillary analyses to be run between the intervention and control arms include a proportion test for the patient’s readiness for hospital discharge. Additionally, an evaluation of feasibility, acceptability, and satisfaction will be summarized for inclusion when discussing the cost or benefit of the intervention.

Using intent-to-treat, participants providing data at baseline and first check-in will be included. Missing data (eg, due to attrition) will be accounted for using multiple imputations via the mice package in R (R Core Team) [38]. Sensitivity to missing data will be assessed by comparing multiple imputations to complete case analyses.

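### Depression is a descriptive outcome in the Methods, but the Discussion expects significantly fewer positive screens than in the control arm, and no between-arm test is named for it

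*Protocol article*

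**What the plan says.** Three sections of the protocol article bear on the depression outcome.

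- **Data Collection or Measures** sets its status: "Other descriptive outcomes include postpartum health status, which will include measures of postpartum depression, stress, complications experienced, vital signs". It describes the EPDS as "a self-report screening tool commonly used in perinatal settings" and gives its range and direction: "The EPDS has a maximum score of 30, with higher scores indicating higher frequency and increased severity of depressive symptoms". No cut-off for a positive screen is given.
- **Analysis Plan** says how health status is analysed: "For the intervention arm, follow-up secondary analyses will measure the change in postpartum health status, postpartum health behaviors, and clinical assessment data over time", by repeated measures MANOVA. The expectations in that section concern knowledge of warning signs and health behaviors ("We expect postpartum health behaviors to be different between the intervention and control arms"); depression is not named. A test of proportions appears once, for readiness for hospital discharge.
- **Principal Findings** (Discussion) says that "we also expect mental health outcomes such as positive depression screens to be significantly lower over time in the Focused-PPC group compared to the control" arm.

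Table 1 collects the EPDS at baseline, 1-2 weeks, 6 weeks, 3, 6 and 12 months. The sample size rests on the knowledge score alone.

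**The concern.** The Discussion sentence sets out a result to be judged by a significance test between arms. The Methods class the same outcome as descriptive and plan an analysis that leaves out the control arm. An analyst cannot follow both. A fall in EPDS within the intervention arm would not answer the stated expectation, because scores may change over the postpartum year in the control arm as well.

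The form of the outcome is also unsettled. The Methods describe a 0 to 30 scale and the Discussion speaks of screens that are positive or not. If the arms are to be compared, this choice affects how much the trial can detect with 96 women per arm. The primary outcome and the sample size are untouched. What is at stake is whether a claim about depression at the end of the trial would rest on an analysis planned for it.

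**Working it through.** **1. Status and test, section by section.**

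| Section | Status of depression | Form | Comparison |
|---|---|---|---|
| Data Collection or Measures | descriptive | EPDS, maximum 30; also called a screening tool | none stated |
| Analysis Plan | follow-up secondary analysis of health status | not stated; MANOVA | change over time, intervention arm only |
| Principal Findings | significant difference expected | positive screens, given as an example | intervention against control |

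The last row agrees with neither of the others on status, and its comparison appears in neither.

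**2. The plan's own sample size figure.** It concerns knowledge only. With Cohen f = 0.15, m = 3 measurements, correlation 0.3 and N = 192, the noncentrality of the between-arm F test is f²·N·m / [1 + (m − 1)·0.3] = 0.0225 × 192 × 3 / 1.6 = 8.1. Power is 0.808, and the smallest N reaching 0.80 is 188. So 192 reproduces, but it says nothing about the EPDS.

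**3. Score against screen, under stated assumptions.** From the article: 192 women allocated 1:1, so 96 per arm, and a type I error of 0.05. Assumed: two-sided testing, one time point, no attrition, a normally distributed score and a standardised difference d = 0.30. For two equal groups d = 2f, so this is the size of f = 0.15, borrowed from the knowledge outcome for illustration.

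Score: noncentrality = d·√(n/2) = 0.30 × √48 = 2.078 on 190 degrees of freedom, with critical value 1.973. Power = 0.54.

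Positive screen: let p0 be the control rate and z its upper normal quantile. The same shift gives p1 = P(Z > z + 0.30). The standard error is √{[p0(1 − p0) + p1(1 − p1)]/96}, and power is Φ[(p0 − p1)/SE − 1.96]. Relative efficiency is φ(z)²/[p0(1 − p0)].

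| p0 (assumed) | p1 | (p0 − p1)/SE | Power | Ratio to 0.543 | Relative efficiency |
|---|---|---|---|---|---|
| 10% | 5.7% | 1.115 | 0.20 | 0.37 | 0.34 |
| 15% | 9.1% | 1.268 | 0.24 | 0.45 | 0.43 |
| 20% | 12.7% | 1.378 | 0.28 | 0.52 | 0.49 |
| 30% | 20.5% | 1.527 | 0.33 | 0.61 | 0.58 |

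**4. Range.** Under the normal model, with d from 0.2 to 0.5 and control rates from 5% to 50%, the power ratio runs from 0.25 to 0.83. With an assumed skewed (gamma) score, mean 5 to 7, SD 4 to 5, cut-offs 10 to 13 and d of 0.3 or 0.4, it runs from about 0.5 (0.27/0.55) to 0.9 (0.71/0.79). The score has the higher power throughout, but the margin depends on inputs that the article does not give.

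**The case against.** The strongest reply is that this is one sentence of expectation in a Discussion, about an outcome that is neither primary nor secondary, in an article that condenses a fuller protocol. Several parts of that reply stand.

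- A reader might infer that the article gives the EPDS two contradictory endpoint definitions. It does not. The Methods call the EPDS a screening tool and never say that the total score is what will be analysed. The Discussion offers positive screens only as an example of mental health outcomes. Naming MANOVA does not settle the form either, because the same sentence covers health behaviors, some of which the Discussion describes in yes/no terms. Score or screen is an open choice.
- A reader might infer that the missing cut-off leaves the team free to pick a favourable one. In one simulation under an assumed skewed score, free choice among four cut-offs raised the false-positive rate at one time point from 5% to about 11%. But an article may leave a cut-off to the full protocol or SAP, and nothing here shows that it is unfixed there.
- A reader might infer that the yes/no version has about half the power. That holds under the normal model at control rates near 15% to 25%, but it is not a fact about this trial.

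It can also be said that the Analysis Plan opens with a general intention to assess outcome differences between arms. That sentence names no method, and the specific sentence on health status confines the analysis to the intervention arm.

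The reply does not remove the conflict of status or supply the missing comparison. Those lie in what the article itself states, and a fuller document would have to depart from one passage or the other.

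**Conclusion.** The point holds in limited form. The article assigns depression a descriptive status and a within-arm analysis, then expects a significant between-arm difference; this rests on the text alone. The preference for the score as the compared measure rests on assumptions: power of about 0.54 against 0.20 to 0.33 at d = 0.30, with a ratio between about 0.25 and 0.9 over the inputs tried. Those figures are for a single time point, whereas the expectation concerns change over time with five follow-up measurements, so they indicate direction rather than the power of a longitudinal analysis. The primary analysis and the sample size are not affected.

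**What to change.** In the Analysis Plan, name the depression analysis: a between-arm comparison of EPDS total score over follow-up, adjusted for baseline EPDS. Table 1 already collects that baseline, and the Randomization section places the baseline survey before allocation, so it is a sound covariate. Report the proportion of positive screens by arm as supportive, at one cut-off fixed before arm-level data are examined. Then align the status in Data Collection or Measures and the expectation in Principal Findings with this analysis.

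If depression is meant to stay descriptive, drop the word implying significance from Principal Findings instead.

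No new data are needed. The first route costs one additional secondary analysis and leads with a measure less directly clinical than a screen-positive rate, which is still reported. The second route is wording only.

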### Challenges Encountered

A major hurdle the team faced early in the intervention, which impacted the scheduled engagements with the leadership of GHS, was the application and subsequent acquisition of institutional review board clearance from the Navrongo Health Research Center. The clearance was obtained after about 3 months of waiting time, and implementation could not commence unless proof of clearance was presented to the leadership of GHS in the Northern Region for permission to be given for the team to commence implementation. Delays in reviewing the Focused-PPC guide also contributed to a later than expected start of recruitment. The guide went through multiple levels of review, and reviews took longer at each stage than had been planned. In addition, the project team faced some difficulties finding context-specific audiovisual content to be used as supporting aids during the FPPC sessions. Finding and creating context-specific teaching aids took longer than expected. There have been no protocol modifications to the study so far.

We are consistently monitoring and improving upon data collection as necessary. For instance, following issues with inconsistent participant tracking numbers, our data scientist was able to install a mechanism into our survey software that double-checks each tracking number and will not allow remaining data to be documented until this has been addressed. We have also implemented solutions to address accidental missed data by alerting project assistants in real time if important information is missing, allowing them to review entered surveys before submission, and getting an email confirmation immediately after submitting a survey. Our monitoring efforts on this front have led to more accurate and comprehensive data so far and also improved the process of recording data for our project assistants. Furthermore, we have held monthly meetings with the project team, including all members from both the United States and Ghana. These meetings have helped substantially in prioritizing the goals of the trial and have allowed us to properly deal with obstacles as they arise.

### Anticipated Limitations

Due to the nature of the study described in this protocol, the intervention is not blinded. There may be a potential for contamination since the midwives implementing the study are used in the health centers. However, since the study is not blinded, different midwives provide care and education to women during postpartum visits if they are in the control group to minimize contamination. In addition, the study is being conducted in one municipality in Tamale, so generalizability will be limited. We hope to conduct a larger study in the future. Given that the team in Ghana has worked in the setting since 2009 and has an established relationship with the health centers and women in the communities, we do not anticipate major recruitment difficulties. However, retention of participants and some participants missing scheduled sessions may be a challenge. We will engage participants and call them individually to remind them of upcoming sessions. We will ensure that midwives recap sessions are comprehensive enough to ensure knowledge transfer to those who missed previous sessions.

### Dissemination Plan

To ensure that the results of this research impact practice and maximize the benefit to women, we will target multiple audiences with our research findings. These include health care providers, community service providers, nonprofit organizations, policy makers, the public, academia, and pregnant and postpartum women. We will prepare, print, and share information notes about the project and its findings and share these among key stakeholders. We will also produce a 5-minute video documentary of the project that demonstrates what was done at each stage of the project and the ultimate outcomes. This project’s video documentary would be widely disseminated through various web-based and offline platforms. Our dissemination plan includes (1) peer-reviewed manuscripts, (2) peer-reviewed presentations at prestigious conferences, (3) presentations to stakeholders, (4) media releases, blog or website posts, (5) technical and research reports, and (6) presentations to postpartum women at the study facilities during postnatal care gatherings as well as community dissemination.

### Conclusions

This project will be the first of its kind to implement an integrated and comprehensive group postpartum care delivery model in Ghana, focused on the care of the mother in addition to the baby. Focused-PPC has the potential to change the postpartum care delivery model in Ghana and other countries in sub-Saharan Africa and beyond. Results from this implementation will be used to further refine and scale up the Focused-PPC model of postpartum care.

## Abbreviations

EPDS: Edinburgh Postnatal Depression Scale
Focused-PPC: Focused Postpartum Care
GHS: Ghana Health Service
MANOVA: multivariate ANOVA
PSS: Perceived Stress Scale
RHDS-NM: Readiness for Hospital Discharge Scale – New Mother Form
WHO: World Health Organization
